### Economic evaluation

Data for the economic analysis is collected via patients and from hospital records. Table 2 summarizes the data collection for the economic evaluation. As valid information on the resource use can only be retrospectively gathered for a short previous time period the assessment of resource utilization is conducted quarterly.

**Table 2 T2:** Overview on the cost categories, the measurement of the resource use and its valuation

Cost category	Resource use	Valuation
Outpatient care	Number of consultations	€ per consultation
Prescribed drugs	Central pharmaceutical number, ATC code, dose rate	Pharmacy retail price
Inpatient care	Length of stay and number of days on the intensive care unit, if applicable DRG	Daily hospital rate, if applicable DRG
Rehabilitation (excluding primary rehab)	Length of stay	Daily rehabilitation rate
Remedies (physiotherapy, massage)	Number of visits	Average rates
Ambulatory care	Days per week and performed activities (or hours per day)	Average rates for activities (or hours)
Home help	Hours per week	Average labor costs for a home help
Informal care	Care level declared by the long term care insurance	Max amount paid by the long term care insurance if the patient does not make use of formal care

Within the last years, standardized instruments measuring the resource use were developed such as the RAI (Resident Assessment Instrument) [21] or the RUD (Resource utilization of dementia) [22]. Based on these questionnaires and on our experiences we developed a questionnaire for the patients that can be used in personal and telephone interviews.

The valuation of the resource use will be based on the valuation rates calculated by Krauth et al. [23]. As the valuation rates are based on data for the year 2000 the calculations will be up-dated.

Especially in the economic evaluation of interventions with the elderly informal care plays an important role. However, as the assessment is very time consuming and the interview time should be minimized we refrained from assessing informal care time. To estimate the cost of informal care we use the information on a care level declared by the long term care insurance. If the patient is allowed to receive nursing care and does not receive formal care, it is assumed that the patient has an informal caregiver. In that case, the maximum amount for care at home paid by the long term care insurance will be used as cost for informal care.

Cost for the intervention excluding the costs caused by the study will be considered. Cost components will include labor costs, travel expenses, telephone costs etc.

In order to calculate quality-adjusted life years (QALYs), the EQ-5D questionnaire [24] is applied at baseline, at interim telephone contacts, and during the final assessment. Additionally, the Visual Analogue Scale (VAS) [24] is applied at baseline and final assessment.

It is planned to perform a cost-utility-analysis from the societal perspective. This means that incremental costs of the intervention (vs. control) are set in relation to the number of QALYs gained. The resulting incremental cost-effectiveness ratio (ICER) is an international standard for reporting results of economical evaluation studies. In addition, we will calculate additional costs per life year saved and per year without event. For the estimated ICER value a 95% confidence interval will be calculated based on bootstrap methods.

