## Abstract

**Background:**

Aged patients with coronary heart disease (CHD) have a high prevalence of co-morbidity associated with poor quality of life, high health care costs, and increased risk for adverse outcomes. These patients are often lacking an optimal home care which may result in subsequent readmissions. However, a specific case management programme for elderly patients with myocardial infarction (MI) is not yet available. The objective of this trial is to examine the effectiveness of a nurse-based case management in patients aged 65 years and older discharged after treatment of an acute MI in hospital. The programme is expected to influence patient readmission, mortality and quality of life, and thus to reduce health care costs compared with usual care. In this paper the study protocol is described.

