Due to changes in the German health care system, in particular the establishment of the diagnosis related groups (DRG) system, older patients with complex health care needs are nowadays discharged earlier from hospital than a few years ago [11]. For many of these patients an optimal care at home is not guaranteed, resulting in subsequent readmissions or final admission to a nursing-home. Medication compliance and lack of medication-related knowledge are serious problems in aged patients, and in higher age-groups there is also often a lack of social support or knowledge to seek medical support promptly, when specific symptoms appear [12]. Thus, optimizing care for this population has a high priority.

Many hospital admissions among aged patients with CHD can be attributed to behavioural and social factors rather than to deteriorating cardiac function or an intercurrent cardiac event [13]. Thus, aged multimorbid patients at risk of poor outcomes might benefit from intensive home follow-up. A nurse-led home-based intervention program including patient education and counselling might improve medication compliance, medication-related knowledge and thus processes of care, coronary risk factor profiles, functional status, and quality of life. As a consequence, this might reduce mortality. In addition, such a program is expected to reduce health care resource use in patients with CHD and consequently total health care expenditures.

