## Methods/Design

### Study design

The study is designed as a single-centre randomized two-armed parallel group trial. The study is carried out within the framework of KORA (Cooperative Health Research in the Region of Augsburg). All patients receive a baseline assessment after giving their informed consent. The baseline assessment is carried out by the study physician and a study nurse. Those who are subsequently randomized to the intervention group receive the intervention starting with the initial session shortly before discharge (see Figure 1). All patients are contacted by phone after 3, 6, and 9 months in order to document a core set of relevant outcome measures. The duration of the intervention phase is one year. After one year a final investigation takes place in the hospital or at home.

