## Discussion

This paper describes the study design of the KORINNA study, an innovative randomized controlled trial evaluating the effectiveness of a nurse-based case management programme for old-aged patients with MI. The KORINNA study is unique in a twofold way.

First, the nurse-led case management is tailored to the specific needs of old-aged people with MI. The interventions specifically address common challenges and risks associated with the MI management in elderly people such as multi-morbidity and compliance with medication. Further, the programme is flexible regarding frequency and location of the intervention. Thus, when deciding on the number of interventions necessary or whether a home-visit or telephone call is more appropriate, the nurse can take the individual health and living condition of a patient into account. Our experiences gathered from approximately 100 patients who have already received interventions within the study, confirm the need for a highly individualized intervention programme. Until now, a broad range of health states and impairments among the study participants could be observed which necessitates a variable intervention intensity.

Second, a particular strength of this study relates to the planned economic evaluation. In view of scarce financial resources within the German health system it is essential that innovative models of care not only demonstrate positive effects on clinical and patient-related outcomes but also cost-effectiveness. Since cost savings have already been shown in comparable studies in other countries, the economic results of this study are highly anticipated.

A possible limitation of the study design refers to the relatively short follow-up interval of one year. It is still unclear whether the expected positive intervention effects on readmission to hospital or death can already be observed within this time interval. Hence, a prolongation of the study with a follow-up interval of 3 years is already taken into consideration. A further limitation of the study is its single center design.

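### The bootstrap 95% interval on the ICER is not a reliable basis for a decision if the one-year QALY difference straddles zero; incremental net benefit from the same replicates would be

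*Protocol article*

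**What the plan says.** The Economic evaluation section plans a cost-utility analysis from the societal perspective in which "incremental costs of the intervention (vs. control) are set in relation to the number of QALYs gained". On uncertainty it commits to one thing: "For the estimated ICER value a 95% confidence interval will be calculated based on bootstrap methods". It also states that "we will calculate additional costs per life year saved and per year without event", without saying whether those ratios will carry intervals.

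On direction, the Abstract says: "The programme is expected to influence patient readmission, mortality and quality of life, and thus to reduce health care costs compared with usual care". The Background repeats that "such a program is expected to reduce health care resource use in patients with CHD and consequently total health care expenditures", and the Discussion recalls savings in earlier work: "Since cost savings have already been shown in comparable studies in other countries".

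On the horizon, the Study design section says: "The duration of the intervention phase is one year". The Discussion concedes: "It is still unclear whether the expected positive intervention effects on readmission to hospital or death can already be observed within this time interval".

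The article gives no expected QALY difference, cost difference, standard deviation, correlation or willingness-to-pay value.

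**The concern.** A ratio of two differences carries a usable interval only while its denominator stays clear of zero. If it does not, two problems follow.

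- The sign of the ratio no longer identifies the result. A negative ICER arises when the programme is better and cheaper, and also when it is worse and dearer. A positive one arises when it is better and dearer, and also when it is worse and cheaper.
- Replicates with a QALY difference near zero produce enormous ratios of either sign, and these set the limits.

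A third problem remains even when the denominator is safely positive. If cost falls, the ICER is negative and its size does not rank results from worse to better.

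At stake is what decision makers can read from the economic result, which the Discussion presents as a particular strength of the study. The primary endpoint and the sample size are not involved.

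**Working it through.** **1. The plan's own figure.** Two proportions, 40% against 25%, two-sided 5%, 80% power, no continuity correction: 152 per group, power 0.800. With 10% dropout, 152/0.9 = 168.9, so 169 per group and 338 in total. The stated sample size reproduces. I use 152 per arm below.

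**2. How large might the QALY difference be?** The article does not say. From its event rates, 0.40 - 0.25 = 0.15 fewer events per patient. Assume each averted event saves half a year at a utility loss of 0.05 to 0.20: 0.15 × 0.5 × 0.05 = 0.004, up to 0.15 × 0.5 × 0.20 = 0.015 QALY. As a ceiling, if every averted event were a death at utility 0.8: 0.15 × 0.5 × 0.8 = 0.06.

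**3. How precisely is it measured?** SE = SD × √(2/152). QALY SDs of 0.15 to 0.30 are assumed.

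| QALY SD | SE | True +0.02: share below 0 | True +0.02: P(95% CI includes 0) | True +0.05: share below 0 | True +0.05: P(95% CI includes 0) |
|---|---|---|---|---|---|
| 0.15 | 0.017 | 12% | 79% | 0.2% | 17% |
| 0.20 | 0.023 | 19% | 86% | 1.5% | 41% |
| 0.25 | 0.029 | 24% | 89% | 4% | 59% |
| 0.30 | 0.034 | 28% | 91% | 7% | 69% |

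A denominator that straddles zero is therefore likely, though not certain.

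**4. When does the ratio agree with the decision?** Write e for the QALY difference, c for the cost difference and λ for the threshold. Net benefit is λe - c. If e > 0, then c/e < λ is equivalent to λe - c > 0, so the upper limit can be read against λ. If e < 0, dividing by e reverses the inequality: c/e < λ then means net benefit is negative. Replicates with e < 0 that fall below the threshold are exactly those with a net loss.

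**5. Illustration.** Bivariate normal draws of (e, c) stand in for the bootstrap cloud. Assumed: 152 per arm, cost SD EUR 9,000, correlation -0.3, λ = EUR 30,000. SE of the cost difference = 9,000 × √(2/152) = 1,032. With QALY SD 0.20 (SE 0.0229), SE of net benefit = √[(30,000 × 0.0229)² + 1,032² + 2 × 0.3 × 30,000 × 0.0229 × 1,032] ≈ 1,402.

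- *+0.02 QALY, -EUR 500.* Better/cheaper 59%, better/dearer 22%, worse/cheaper 10%, worse/dearer 9%. Percentile limits of the ICER are about -400,000 to +370,000. About 13% of the negative ratios come from the worse-and-dearer quadrant. Net benefit = 30,000 × 0.02 + 500 = 1,100; 1,100/1,402 = 0.785, so the probability of cost-effectiveness is 0.78.
- *+0.05 QALY, -EUR 1,000.* About 83% better/cheaper. Limits are about -102,000 to +43,000. Net benefit = 30,000 × 0.05 + 1,000 = 2,500; 2,500/1,402 = 1.78, probability 0.96.
- *+0.01 QALY, no cost difference.* The share of ratios below 30,000 is 0.76. Net benefit = 300; 300/1,402 = 0.214, probability 0.58. The ratio overstates the case for the programme.
- *+0.05 QALY, -EUR 1,000, QALY SD 0.15.* Only 0.2% of draws have e < 0. The share of ratios below 30,000 and the probability of positive net benefit are both 0.974.

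Varying the assumptions at +0.02 QALY (QALY SD 0.20 to 0.25, cost SD EUR 8,000 to 12,000, cost difference -1,000 to +500, correlation -0.2), the limits range from about -317,000/+315,000 to about -633,000/+554,000, and the cloud covers all four quadrants each time.

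**6. Ordering of negative ratios.** -1,000/0.02, -2,500/0.05 and -500/0.01 all equal -50,000, and so does the dominated pair +500/-0.01. At a fixed saving of 1,000, raising the gain from 0.02 to 0.05 moves the ratio from -50,000 to -20,000, so more health looks like a weaker result.

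**The case against.** The strongest reply has four parts.

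First, a reader might infer that expecting lower cost with better outcome is enough to make the interval uninterpretable. It is not. While nearly all replicates show a QALY gain, the ratio and net benefit give the same decision, as step 4 and the 0.974 agreement in step 5 show. This stands. What is lost in that case is the meaning of the lower limit, not the use of the upper one.

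Second, a reader might take it as given that the QALY difference will be near zero, or that a net societal saving is planned for. The article states neither. The savings it expects are in health care costs, whereas the ICER is societal and adds programme labour, travel and telephone costs. This also stands, so the point must be conditional.

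Third, the article says only that bootstrap methods will be used and does not name the percentile method. That is correct but does not rescue the plan. No ordering of the ratio alone can separate dominant from dominated replicates once the denominator changes sign.

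Fourth, a condensed article may leave the cost-effectiveness plane, acceptability curve or threshold range to the full protocol. That is fair, and their absence is not the complaint. The point concerns the interval to which the article does commit.

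**Conclusion.** The point holds in conditional form. If the replicates straddle zero on QALYs, the planned interval mixes opposite conclusions and does not support a decision; at +0.02 QALY the limits run to several hundred thousand euro each way. If nearly all replicates show a gain, the upper limit is usable. A negative lower limit is not, and the better-and-cheaper quadrant is where the expected savings point if they exceed the cost of the programme.

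The algebra in steps 4 and 6 needs no assumptions. The likelihood of straddling zero and all euro figures rest on the assumed SDs, correlation, differences and threshold.

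Two stronger readings are not supported. The interval is not invalid in every multi-quadrant case. Cost-utility is not the main secondary objective either: the objectives section lists it without ranking, and the Abstract names cost-effectiveness last. Severity is moderate. The primary endpoint and sample size are unaffected, and the Analysis section treats secondary outcomes as exploratory.

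**What to change.** Reword the uncertainty statement in the Economic evaluation section so that, from the same bootstrap replicates, the report gives:

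- incremental cost and incremental QALYs, each with a 95% interval;
- incremental net monetary benefit with a 95% interval over a prespecified range of willingness-to-pay values, as the stated uncertainty measure;
- the cost-effectiveness plane and the acceptability curve.

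Report the ICER as a point estimate when both differences are positive. When the signs are opposite, say which arm dominates. If both are negative, say so and rely on the two differences and net benefit. Give an interval for the ratio only if essentially all replicates show a QALY gain at higher cost. If intervals are intended for the ratios per life year saved and per event-free year, apply the same rules to them.

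The cost is a change of analysis wording, best made before the data are seen. It needs no new data, patients or resampling.

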### Analysis

The statistical analysis for the primary endpoint will focus on the null hypothesis that there is no difference between intervention and control with respect to the distribution of time to un-planned readmission (including out-of-hospital death). This hypothesis will be statistically tested using a Cox proportional hazards model including age, gender, and comorbidity as covariates.

Statistical analyses for secondary outcomes will be based on (generalized) linear models depending on the type and distribution of the outcome variable. Since these will be multiple tests for which control of the overall error level cannot be achieved, these will be regarded as exploratory analyses. All analyses will be done according to the intent-to-treat approach.

### Sample size

Based on a comparable study by Young and colleagues [25] with patients 70 years of age we expect an event rate (readmission or out-of-hospital death) of 40% in the control group. If the study is designed to have 80% power or more to detect an improved rate of 25% in the intervention group (i.e. Δ = 0.15) at a two-sided type I error level of 5%, at least 152 patients per group will be needed. We expect that the drop-out rate does not exceed 10% during the 1-year follow-up period. In order to allow for loss to follow-up (patient withdrawing consent or moving away from study region), it is planned to recruit a total of 338 patients for the trial.

## Discussion

This paper describes the study design of the KORINNA study, an innovative randomized controlled trial evaluating the effectiveness of a nurse-based case management programme for old-aged patients with MI. The KORINNA study is unique in a twofold way.

First, the nurse-led case management is tailored to the specific needs of old-aged people with MI. The interventions specifically address common challenges and risks associated with the MI management in elderly people such as multi-morbidity and compliance with medication. Further, the programme is flexible regarding frequency and location of the intervention. Thus, when deciding on the number of interventions necessary or whether a home-visit or telephone call is more appropriate, the nurse can take the individual health and living condition of a patient into account. Our experiences gathered from approximately 100 patients who have already received interventions within the study, confirm the need for a highly individualized intervention programme. Until now, a broad range of health states and impairments among the study participants could be observed which necessitates a variable intervention intensity.

Second, a particular strength of this study relates to the planned economic evaluation. In view of scarce financial resources within the German health system it is essential that innovative models of care not only demonstrate positive effects on clinical and patient-related outcomes but also cost-effectiveness. Since cost savings have already been shown in comparable studies in other countries, the economic results of this study are highly anticipated.

A possible limitation of the study design refers to the relatively short follow-up interval of one year. It is still unclear whether the expected positive intervention effects on readmission to hospital or death can already be observed within this time interval. Hence, a prolongation of the study with a follow-up interval of 3 years is already taken into consideration. A further limitation of the study is its single center design.

So far, we have experienced an unexpected challenge regarding the number of eligible patients aged 75 years and older. Some months after starting recruitment it became apparent that the planned sample size cannot be reached within the expected time frame. We discussed this problem with the members of the studies' advisory board and decided to decrease the minimum age of study participants from 75 years to 65 years. As a consequence of the initially low number of patients who could be included in the study, the recruitment phase will be extended by several months. In addition, the number of patients who could not be included due to severe concomitant diseases or dementia (20%), or since they were already nursing home residents (10%), was higher than expected. On the other hand, the number of study patients who were lost to follow-up within the one-year treatment course currently is 7% and therefore even lower than initially expected. In addition, we have noticed that the home visits as well as telephone calls are very well accepted by the patients. These findings indicate a good acceptance and feasibility of the study.

In summary, the KORINNA study is expected to contribute to the evidence regarding the effectiveness of nurse-based case management programmes for aged patients with MI. The results can be an important basis for clinicians, administrators and health policy makers to decide on the provision of high-quality care to older patients with MI.
